## Aims and hypotheses

The primary aim of this study was to evaluate whether our specialized stepped care service for BPD patients, namely, the STP-BPD would produce better outcomes for treated patients than would the standard TAU service over a longitudinal 2-year follow-up evaluation at four different time points after participant enrollment. The primary outcomes of this study address the severity of BPD manifestations as well as the symptoms of self-harm and suicidality. Furthermore, we conduct an evaluation of the costs of health care services, as well as an evaluation from a societal perspective. A crucial challenge for BPD-specific health care services would be to improve the general psychopathology; the interpersonal, psychosocial and occupational functions; and the quality of life of patients. These domains are addressed by our study’s secondary outcomes.

Additionally, we will examine the mediating effects of reflective functioning and various aspects related to personality organization, such as defense mechanisms. More specifically, we hypothesize that improvements in reflective functioning during the initial phase of treatment will predict reductions in BPD symptoms and self-injurious behavior at later stages. Age will be treated as a moderator variable in line with evidence regarding the course of the disorder, the symptoms of which, tend to decline with age (49).

In addition to the abovementioned main objectives, this study aims to translate, adapt, and analyze the psychometric properties of the instruments employed in the present research among the Greek population, as some of them have not yet been rigorously evaluated. This investigation is currently in progress for most instruments, apart from those whose Greek versions have already shown satisfactory psychometric properties. Our hypotheses are as follows: 1) Participants receiving specialized stepped care services will exhibit greater clinical improvement, and specialized stepped care services will prove to be more cost-effective than TAU services. 2) Compared with participants receiving standard TAU, those receiving specialized service will exhibit greater functional improvement as well as enhanced QOL. 3) The differences discerned in the outcome variables between the two groups are expected to be mediated by differences in reflective functioning, defense style and personality organization.

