### Mediators

**Reflective Functioning Questionnaire (RFQ**) (88, 89): This is a brief, screening measure of reflective functioning. It has been developed to assess severe impairments or imbalances in mentalizing, which are typically observed in patients with borderline personality disorder features. Through confirmatory factor analyses, the two factors—certainty (RFQ_C) and uncertainty (RFQ_U)—were found to be fairly different. They remained the same across clinical and nonclinical samples and had good internal consistency and test-retest stability. The RFQ has satisfactory reliability and test–retest reliability. The estimates of internal consistency for RFQ_U and RFQ_C were.77 and.65, respectively, in the clinical sample and.63 and.67, respectively, in the nonclinical sample. The test–retest reliability over a period of 3 weeks was excellent, with *r*
_s_ = .84 and.75 for RFQ_U and RFQ_C, respectively, all *p* =0.001 (88).

**Defense Style Questionnaire (DSQ-40)** (90): The 40-item version of the DSQ-40, derived from the original measure developed by Bond, Gardner, Christian, and Siegel (91), is a widely used self-report measure for defense mechanisms because of its easy administration and cost effectiveness. It aims to assess behavior indicative of conscious derivatives of defensive styles that correspond to hypothesized patterns of unconscious psychological mechanisms (90).

The **Inventory of Personality Organization (IPO)** (92, 93) is a self-report instrument intended to measure a patient’s level of personality organization. We constructed the scale to cover five personality dimensions, with the first three serving as the primary clinical scales. These scales assess the degree of identity pathology, the level of immature defensive mechanisms (Primitive Defenses, PD), and the degree of impairment in the ability to test reality (Reality Testing, RT). The three IPO scales demonstrate adequate internal consistency and good test–retest reliability. Lenzenweger (92) reported that the three main dimensions of an IPO’s first psychometric properties in adult and psychiatric samples are internally consistent: identity diffusion (α = .84–.90), reality testing (α = .85–.87), and primitive defenses (α = .80–.87). Confirmatory factor analysis at the item level supported a two-factor structure of the IPO, which is consistent with Kernberg’s model of borderline personality organization (92).

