#### Mediation analysis

Mediation analysis will occur through regression models, path analyses and the Sobel test. For each of the outcomes, three mediation analyses will be performed, with independent variable being the group assignment, In Model 1, the mediator will be reflective functioning, in Model 2, the defense style and in Model 3, the personality organization.

Mediation analysis will occur at T_2_, T_4_, T_6_, T_8_, T_10_ Moderation

In the multiple linear regression models described in the Evaluation of Effect, in the predictor variables, an interaction term between group assignment and age will be inserted as well.

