It merits noting that the evaluation of outcomes on many time points (T1 – T10) as well as the direction of causality, intrinsic in longitudinal designs, adds robustness to the study design. Furthermore, the evaluation of a specific pathway of effect, that is that the intervention group will show better scores at the primary and secondary outcomes because of better scores at the mediator variables, strengthens the internal validity of the study. In other words, the study does not only hypothesize that change will be taking place between the two groups in terms of outcome variables but it also clarifies the path whereby change will be elicited (mediation analysis). Inevitably, and due to non-random allocation, the design could not control for unknown confounding variables, which is a limitation of the design. In conclusion, due to the study taking place in routine clinical practice its external validity is high; however, its internal validity is questioned due to the quasi-experimental design. Consistent efforts have been made to increase its internal validity; however, unknown confounding could not have been addressed for due to reasons intrinsic to the quasi-experimental design.

Moreover, patients’ use of additional therapeutic interventions may also be a confounding factor. However, this study only treats patients at the assigned center. In addition, being a prevalent user is classified as an exclusion criterion, which minimizes inception bias (102).

Finally, bias arising from deviations in the care provided from the intended intervention is referred to as performance bias (102). This limitation can be addressed by precisely defining the treatment provided. Nevertheless, no matter how strictly an intervention is defined, there will inevitably be some variation due to possible differences in the experience of care providers. Furthermore, due to treatment for BPD being a complex heath intervention (94) it is hard to disentangle the effects of the content of the intervention, the duration and intensity of treatment. Information on these elements will be gleaned and treated as confounder variables in the model.

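### Three separate single-mediator models cannot tell a specific mechanism from a correlated proxy, although two of the mediators overlap by the protocol's own description

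*Protocol article*

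**What the plan says.** The Mediation analysis section sets the structure: "For each of the outcomes, three mediation analyses will be performed, with independent variable being the group assignment". It then assigns one mediator to each model: "In Model 1, the mediator will be reflective functioning, in Model 2, the defense style and in Model 3, the personality organization". The methods are given as follows: "Mediation analysis will occur through regression models, path analyses and the Sobel test".

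Hypothesis 3 (Aims and hypotheses) names all three together. The group differences "are expected to be mediated by differences in reflective functioning, defense style and personality organization". The same section speaks of "various aspects related to personality organization, such as defense mechanisms", which places defenses within personality organization.

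The Mediators section describes the DSQ-40 (Model 2) as a self-report measure of defense mechanisms. It lists, among the primary clinical scales of the IPO (Model 3), one for "the level of immature defensive mechanisms (Primitive Defenses, PD"). Table 1 schedules RFQ, DSQ-40 and IPO at the same visits (T0, T2, T4).

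Limitations and challenges uses the result as evidence of mechanism and as support for internal validity: "it also clarifies the path whereby change will be elicited (mediation analysis").

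**The concern.** A model with one mediator credits that scale with whatever part of the effect runs through correlated mediators left out of the model. This is omitted-variable bias, so correcting for multiplicity or replacing the Sobel test with a bootstrap does not remove it. Where two scales share content, as the DSQ-40 and the IPO do here, a significant result for one may simply reflect the other.

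At stake is hypothesis 3 and the mechanistic reading in Limitations and challenges. The trial could name defense style as a route of change when personality organization is the route, or the reverse. The separate indirect effects can also add up to more than the indirect effect that exists.

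**Working it through.** **Inputs from the protocol article.** N = 212 (106 per group) and d = 0.45 (Sample size); two-sided 5% (Statistical analyses); Sobel test and one mediator per model (Mediation analysis).

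**The plan's own figure.** A two-sample t-test with d = 0.45 and power 0.90 needs 104.7, so 105 per group (210 in total), against the stated 106 (212). The figure reproduces. The article gives no figure for the mediation analysis.

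**Assumptions, not in the document.** Within-group correlation r between mediators of 0.3, 0.5 or 0.7. The working mediator M1 is shifted 0.45 SD by the service and acts on the outcome with slope b = 0.4 (checked also at 0.3 and 0.5). An inert scale M2 has no effect of its own and is shifted by a2, which is 0.45 (equal shift), 0.45r (carried over through the correlation) or 0 (none).

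**Algebra.** In its own model M2 receives a slope of b·r, so its apparent indirect effect is a2·b·r; the truth is 0. The true indirect effect through M1 is 0.45 × 0.4 = 0.18. At r = 0.5:

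- Equal shift: 0.45 × 0.4 × 0.5 = 0.09 for each inert scale. With two inert scales the three estimates sum to 0.18 + 2 × 0.09 = 0.36, twice the truth.
- Carried-over shift: 0.225 × 0.4 × 0.5 = 0.045 each, sum 0.27.
- No shift: 0 each, sum 0.18.

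**Simulation** (2,000–3,000 runs per setting, N = 212, Sobel at two-sided 5%): share of trials in which a given inert scale is significant.

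| r | Separate, equal shift (b = 0.4) | Separate, carried-over shift (b = 0.4) | Separate, no shift (b = 0.3–0.5) | Joint (b = 0.4) |
|---|---|---|---|---|
| 0.3 | 21% | 1% | under 1% | 1–2% or less |
| 0.5 | 57% | 14% | under 3% | 1–2% or less |
| 0.7 | 81% | 50% | at most 3.4% | 1–2% or less |

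Varying b from 0.3 to 0.5 with an equal shift gives 11–32%, 36–74% and 62–87% at the three correlations. The joint model stays at about 2% or less throughout. At N = 158, the smaller sample named in the Sample size section, the pattern is the same with lower rates (up to 71%).

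**What a joint model costs.** Power for the real mediator at b = 0.4 goes from about 88% to 86% at r = 0.5, and from 88% to 79% at r = 0.7. At b = 0.3 and r = 0.7 it goes from 84% to 64%. With assumed reliabilities of 0.7 for the working scale and 0.85 for the others, it goes from 71% to 46% at r = 0.7.

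**Where a joint model misleads.** In a serial chain (service to M1 to M2 to outcome; M1 to M2 0.5–0.7, M2 to outcome 0.4–0.5), the genuine upstream mediator M1 is detected in about 56–86% of trials in its separate model but 1–2% in a parallel joint model. When two mediators both act equally (r 0.5–0.7), detection of each falls from 86–89% to 35–70%.

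**The case against.** - **Correlation alone is not enough.** A reader might infer that any scale correlated with the working one will be declared a mechanism. The calculation does not support that: the service must also shift the scale. With no shift the rate stays below 4%, and at r = 0.3 with a carried-over shift it is about 1%. This stands and is why the result is a range.
- **Overlap is documented for two scales only.** The article ties defense style to personality organization. It does not say that the RFQ overlaps with either, and it gives no correlation between any of the scales. A reader might also infer that the DSQ-40 and the IPO Primitive Defenses scale measure the same thing. The Mediators section supports only shared content: the DSQ-40 covers defensive styles generally, the IPO scale the immature ones.
- **A joint model is not simply better.** It can hide a mediator that acts through another, and it costs power. Aims and hypotheses expects early gains in reflective functioning to predict later symptom change, so an ordered chain is plausible. This stands, and it argues against replacing Models 1–3.
- **Path analysis is already planned, and hypothesis 3 does not say that each mediator acts independently.** Both are true. But the sentence defining the models still puts one mediator in each, and Limitations and challenges goes further than hypothesis 3 by claiming that the path is clarified. The general acknowledgement there that stronger methods and a statistician's input are needed does not change the stated models.

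**Conclusion.** The point holds in a limited form. As specified, the three models can show that a scale carries part of the service effect or stands in for something that does; they cannot say which. Under the assumed values an inert but shifted scale is significant in about 14–57% of trials at r = 0.5 and 50–81% at r = 0.7, against about 1% jointly. At r = 0.3 the range is about 1–21%. The correlations, effect sizes and shifts are all assumptions. An equal shift is the adverse end, though hypothesis 3 does expect the groups to differ on all three mediators.

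A reader might infer that all three scales will be confirmed whenever one works, or that the effectiveness and cost conclusions are affected. Neither follows. The first would need substantial correlations and shifts for every scale, which the article does not document. The second concerns analyses that do not use these models. The problem is confined to claims of a specific mechanism.

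**What to change.** Keep Models 1–3. For each outcome add one path model with reflective functioning, defense style and personality organization as parallel mediators with correlated residuals, and report specific and total indirect effects. State in advance how the shared defense content is handled, for example by a sensitivity run without the IPO Primitive Defenses scale. Claim a specific mechanism only where the joint model supports it; otherwise call a significant single-mediator result non-specific mediation. Reword the sentence on the path of change in Limitations and challenges to match.

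Cost: analysis wording only. The data are already to be collected and path analysis is already named, so this is a cheap improvement. The downside is lower power per specific pathway: about 2 points at r = 0.5 and 9 at r = 0.7 with b = 0.4, and 20 or more at r = 0.7 with a weaker effect or unreliable scales. The report should say that a null specific effect does not rule out a mediator acting through another one, and that the joint model does not remove unmeasured confounding in this non-randomized design.

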We designed this study to evaluate the effectiveness and economic aspects (cost-effectiveness and cost-utility) of the STP-BPD in everyday clinical practice, adhering to the call for *‘real-world’* clinical trials (55, 56). Therefore, we will use minimal exclusion criteria without altering clinical decision-making, health care, or treatment. Patients will be followed for 2 years for primary and secondary outcomes, and for additional 3 years for primary outcomes only. Assessment of the clinical and psychosocial outcome variables will be performed at baseline (T_0_), prior to patient allocation, and every 6 months until the end of the 2^nd^ year of follow-up (T_1_, T_2_, T_3_, and τ_4_). At baseline (T0) and then every year thereafter (τ2 and τ4), the mediators that affect the link between the type of health care service and the major clinical and psychosocial outcomes will be examined. For long-term evaluation, primary outcome variables will also be assessed at T_5_ (2 years and 6 months), T_6_ (3 years), T_7_ (3 years and 6 months), T_8_ (4 years), T_9_ (4 years and 6 months) and T_10_ (5 years). Patient flow, screening and assessments are displayed schematically in **Figure 1**.

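### Mediation is listed at T6, T8 and T10, but mediators and secondary outcomes stop at T4; 45 of 105 implied analyses have no outcome data and the mediator–outcome lag is not stated

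*Protocol article*

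**What the plan says.** **Planned analyses.** The Mediation analysis section says "For each of the outcomes, three mediation analyses will be performed, with independent variable being the group assignment". Reflective functioning, defense style and personality organization are the mediators of Models 1, 2 and 3. The visits are fixed: "Mediation analysis will occur at T_2_, T_4_, T_6_, T_8_, T_10". The method is also fixed: "Mediation analysis will occur through regression models, path analyses and the Sobel test". The section does not say which mediator measurement goes with which outcome visit.

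**Measurement schedule.** The Design section places the mediator assessments as follows: "At baseline (T0) and then every year thereafter (τ2 and τ4), the mediators that affect the link". The RFQ, DSQ-40 and IPO-GR rows of Table 1 agree (T0, T2, T4). On outcomes, the Design section says "Patients will be followed for 2 years for primary and secondary outcomes, and for additional 3 years for primary outcomes only". Table 1 ends every secondary measure at T4 and carries only the two primary measures on to T10.

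**Hypotheses.** Aims and hypotheses expects that "improvements in reflective functioning during the initial phase of treatment will predict reductions in BPD symptoms and self-injurious behavior at later stages". Separately, hypothesis 3 expects the group differences in outcome to be mediated by differences in the three mediators. It states no lag.

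**Initial phase.** In the section on the STP-BPD, the initial phase of the intervention is the reception outpatient clinic, which lasts 6–8 months.

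**The concern.** A mediation analysis at a given visit needs an outcome at that visit and a mediator measured at a suitable earlier time. Three of the five listed visits come after the last mediator measurement and the last secondary-outcome measurement. For secondary outcomes the stated analysis there cannot be done. For primary outcomes it depends on a choice of mediator visit that the text leaves open, so the choice could be made after the data are seen.

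The reflective-functioning hypothesis is about order in time: the mediator changes early and the outcome follows. A mediator and an outcome taken at the same visit cannot show that order, because outcome change may equally have driven mediator change.

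This matters more than usual because allocation is not randomized. The Limitations and challenges section cites the specified mediation pathway as something that strengthens internal validity. It can do so only if the analysis is feasible and ordered in time.

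**Working it through.** The protocol gives no calculated figure for mediation, so the check sets the visit lists side by side.

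**Inputs**
- Mediation visits: T2, T4, T6, T8, T10 (Mediation analysis).
- Mediator visits: T0, T2, T4 (Design; Table 1).
- Secondary-outcome visits: T0 to T4. Primary-outcome visits: T0 to T10 (Design; Table 1).
- Outcome domains: 2 primary and 5 secondary (Design), so 7. Mediators: 3.
- Initial phase: 6–8 months (section on the STP-BPD). T0 comes before allocation (Design).

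**Visit by visit**

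| Visit | Month | Mediator measured | Secondary outcomes measured | Primary outcomes measured | Months since last mediator |
|---|---|---|---|---|---|
| T2 | 12 | yes | yes | yes | 0 |
| T4 | 24 | yes | yes | yes | 0 |
| T6 | 36 | no | no | yes | 36 − 24 = 12 |
| T8 | 48 | no | no | yes | 48 − 24 = 24 |
| T10 | 60 | no | no | yes | 60 − 24 = 36 |

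**Counts** (outcome domains × mediators × visits)
- Implied by the text: 7 × 3 × 5 = 105.
- Mediator and outcome both measured at the visit (T2, T4): 7 × 3 × 2 = 42.
- Secondary outcomes at T6, T8, T10: 5 × 3 × 3 = 45, with no outcome data (45/105 = 43%).
- Primary outcomes at T6, T8, T10: 2 × 3 × 3 = 18, with no same-visit mediator but feasible with a T2 or T4 mediator.
- Feasible if a lagged mediator is allowed: 42 + 18 = 60. Check: 60 + 45 = 105.

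The count is by domain, with each mediator taken as one variable. Subscales would raise the totals but not change which visits lack data.

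**Initial phase.** Mediator visits are at months 0, 12 and 24. None falls after month 0 and by month 8. T1, at 6 months, has no mediator. Change from T0 to T2 therefore mixes the reception phase with the months that follow it.

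**Sobel test.** It treats the estimated indirect effect, the product of a (group to mediator) and b (mediator to outcome), as normal. To see whether this matters, power was simulated with 3,000 datasets per setting, unit residual SDs and no direct effect, comparing Sobel |z| > 1.96 with a 95% Monte Carlo interval excluding zero. The values of a and b and the 74 per arm are assumptions; 106 per arm is the planned size. Repeat runs differ by a few points.

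| a, b | n per arm | Sobel | Monte Carlo |
|---|---|---|---|
| 0.40, 0.25 | 74 | 35% | 56% |
| 0.40, 0.25 | 106 | 61% | 77% |
| 0.50, 0.30 | 74 | 67% | 80% |
| 0.50, 0.30 | 106 | 90% | 95% |
| 0.50, 0.40 | 74 | 79% | 86% |
| 0.50, 0.40 | 106 | 94% | 94% |

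The gain runs from about 20 points to almost none, depending on the assumed inputs.

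**The case against.** The best defense is that most of this is loose wording. The Design section, Table 1 and the Evaluation of effect section all confine late follow-up to the primary outcomes, so a reader can see that secondary-outcome mediation after T4 was not meant. For primary outcomes, mediators that end at T4 make any analysis at T6 to T10 lagged of necessity, which is the early-to-late order the reflective-functioning hypothesis wants. The exact pairing of visits may sit in a fuller protocol or analysis plan. Mediation is also not the primary comparison, and the Limitations and challenges section already concedes that statistical advice and more robust methods are still to come.

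Much of this stands, and it rules out several stronger readings that a reader might infer:

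- *Most of the mediation analyses cannot be run.* No: 45 of 105 lack outcome data, and 60 are feasible once a lagged mediator is allowed.
- *The plan makes the remaining analyses cross-sectional.* Same-visit pairing at T2 and T4 is the natural reading, but the text does not state it.
- *Hypothesis 3 is not tested.* It requires neither a lag nor an initial phase, and it can be examined at T2 and T4 for all seven domains. The test is weak on the order of mediator and outcome, but it is not absent.
- *The initial phase is certainly unmeasured.* The 6–8 months describe the intervention arm only, and TAU has no phases. If the phrase loosely means the first year, T0-to-T2 change covers it.
- *The Sobel test is underpowered at this size.* That depends on effect sizes the protocol does not give, and regression and path analyses are named beside it.

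What the defense does not remove is the conflict in the published text. The Evaluation of effect section restricts its late analyses to the two primary outcomes. The Mediation analysis section carries no such restriction and names visits at which no mediator is collected. That is a stated rule that cannot be followed as written, not a detail left to another document.

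**Conclusion.** The point holds as a conflict between the mediation visits and the measurement schedule. Of 105 implied analyses, 45 cannot be run, 18 need a lagged mediator that is not named, and 42 are feasible at T2 and T4. If those 42 use mediator and outcome from the same visit, they cannot show that mediator change comes first, and hypothesis 3 is then tested only weakly. If the initial phase has the meaning given in the STP-BPD section, no post-baseline mediator measurement falls within it.

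The counts rest on seven outcome domains and on taking the words on outcomes in the Mediation analysis section at face value. The case against the Sobel test rests on its normality assumption, not on a fixed loss of power. The primary group comparison is unaffected. The correction should be made, because the protocol leans on this pathway to support internal validity.

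**What to change.** 1. Limit mediation of secondary outcomes to T4 or earlier.
2. Specify lagged models. The main one takes the T2 mediator to the T4 outcome, adjusted for the T0 mediator, the T0 outcome and the baseline confounders. For the two primary outcomes only, take a named T2 or T4 mediator to the T6, T8 and T10 outcomes.
3. Keep same-visit analyses at T2 and T4 if wanted, but label them as not establishing time order.
4. Replace the Sobel test with bootstrap or Monte Carlo 95% intervals for the indirect effect, which do not assume that it is normal.
5. Reword the reflective-functioning hypothesis to change over the first year (T0 to T2). Alternatively, add the RFQ at the existing T1 visit so that there is a measurement at 6 months.

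Items 1 to 4 and the rewording cost only text and some analysis programming. Adding the RFQ at T1 costs one brief questionnaire at a visit that already takes place, with slight extra burden for patients. The changes fit the planned consultation with a statistician and should be fixed before the mediator data are analyzed.

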Moreover, a longer-term evaluation will take place for both groups but only for the primary outcome variables, as the interview entailing both primary and secondary outcomes is long and by extending the evaluation time frame, we would not want to lose participants at longer follow-ups and risk the emergence of attrition bias.

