**Figure 1 f1:**
[figure not shown]
Flowchart of the study design.

Primary outcomes will be (i) the severity of BPD symptoms and (ii) the severity of self-harm and suicidality. Secondary outcomes will be: (i) psychopathological symptom severity, (ii) quality of life, (iii) quality and intensity of interpersonal relations, (iv) functioning and (v) disability.

Mediator variables will be: (i) reflective functioning, (ii) defense style and (iii) personality organization. In other words, better primary and secondary outcomes for the intervention group as opposed to TAU group are expected to be discerned due to differences in reflective functioning, defense style and personality organization. As the design does not include random allocation of participants in the two arms, baseline measurements of the outcome variables will be considered as confounders for the ensuing measurements. Moreover, the two groups will be compared in terms of the following variables: sex, family status, education status, number of children, profession, living arrangement, physical illness, medication for BPD and prior hospitalize physical illness, medication for BPD and prior hospitalization. Those variables with a statistically significant difference between the two groups, will be considered confounder variables in the design and will be taken into consideration as such in ensuing evaluation points. Moreover, information about the treatment delivered in the two groups will be recorded; namely, duration of treatment, type and number of sessions attended. These will be included as confounder variables in the design.

The Ethics Committees of Eginition Hospital, Medical School of the National and Kapodistrian University of Athens (No. 404/05-07-2021), Attikon Hospital (No. 443 25/08/2021), and Sismanogleion General Hospital (27703/10-12-2021) approved the research protocol. The Clinical Trials.gov website has registered the trial under the ID NCT06392139 (Protocol ID No. 404/06-07-202).

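### Mediation is scheduled at T6, T8 and T10 for every outcome, but the mediators and the secondary outcomes are last measured at T4, and no lag is defined

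*Protocol article*

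**What the plan says.** The Mediation analysis section fixes both the scope and the visits. On scope: "For each of the outcomes, three mediation analyses will be performed", one each for reflective functioning, defense style and personality organization. On visits: "Mediation analysis will occur at T_2_, T_4_, T_6_, T_8_, T_10".

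The measurement schedule is fixed elsewhere in the article:

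- **Mediators.** Design: "At baseline (T0) and then every year thereafter (τ2 and τ4), the mediators that affect the link" are assessed, that is, at T0, T2 and T4. The RFQ, DSQ-40 and IPO-GR rows of Table 1 agree and are empty from T5 to T10.
- **Outcomes.** Design: "Patients will be followed for 2 years for primary and secondary outcomes, and for additional 3 years for primary outcomes only". Aims and hypotheses says the same ("a longer-term evaluation will take place for both groups but only for the primary outcome variables") and gives a reason: a shorter interview, to limit loss to follow-up. In Table 1 only the BPD severity interview and the Suicide and Self-Harm Inventory continue after T4.
- **Late effect analyses.** Evaluation of effect restricts the regressions after T4 to the two primary outcomes. The Mediation analysis section contains no such restriction.

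**The concern.** The analysis text and the data schedule do not fit together. At T6, T8 and T10 the plan calls for a mediator that is not measured at those visits and, on its literal wording, for secondary outcomes that are no longer collected. A later analysis plan could not repair this by adding detail, because the visit list is already set and the data will not exist.

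Mediation is the third study hypothesis. In Limitations and challenges the authors also rely on the mediation pathway to support the internal validity of a non-randomized comparison. If the late analyses are left undefined, someone will have to choose after the fact which mediator measurement to pair with a year 3, 4 or 5 outcome and what to adjust for. Those choices affect the answer and should be made beforehand.

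**Working it through.** **Inputs**

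- Primary outcomes: 2 (Design, below Figure 1: "Primary outcomes will be (i) the severity of BPD symptoms and (ii) the severity of self-harm and suicidality").
- Secondary outcomes: 5 (same place: "Secondary outcomes will be: (i) psychopathological symptom severity, (ii) quality of life, (iii) quality and intensity of interpersonal relations, (iv) functioning and (v) disability").
- Mediator models: 3 (Mediation analysis).
- Mediation visits: 5, namely T2, T4, T6, T8 and T10 (Mediation analysis).
- Measurement times: Design and Table 1.

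The article gives no count of mediation analyses, so there is no stated figure to reproduce. The sample size of 212 does not enter.

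**What is measured at each mediation visit**

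| Visit | Mediators | Primary outcomes | Secondary outcomes |
|---|---|---|---|
| T2 (1 year) | yes | yes | yes |
| T4 (2 years) | yes | yes | yes |
| T6 (3 years) | no | yes | no |
| T8 (4 years) | no | yes | no |
| T10 (5 years) | no | yes | no |

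**Literal reading: all outcomes at all five visits**

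- Total: 3 models × 7 outcomes × 5 visits = 105.
- Mediator and outcome both measured at the visit (T2, T4): 3 × 7 × 2 = 42, or 40%.
- No same-visit mediator (T6, T8, T10): 3 × 7 × 3 = 63, or 63/105 = 60%.
- Of these, no outcome either (secondary): 3 × 5 × 3 = 45, or 45/105 = 43%.
- Of these, outcome measured but only an earlier mediator available (primary): 3 × 2 × 3 = 18, or 18/105 = 17%.

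**Narrow reading: primary outcomes only after T4, as in Evaluation of effect**

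- Total: 42 + 18 = 60.
- No same-visit mediator: 18/60 = 30%.
- No outcome: 0.

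**Sensitivity of the literal reading to the outcome count**

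- Treatment retention added as a sixth secondary outcome: 3 × 6 × 3 = 54 of 3 × 8 × 5 = 120, or 45%.
- The abstract's three primary measures instead of two: 45 of 3 × 8 × 5 = 120, or 37.5%.
- Both changes: 54 of 3 × 9 × 5 = 135, or 40%.

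The 60% is 3 of 5 visits and does not depend on how outcomes are counted.

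**Age of the mediator if a lag is used**

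- From T4 (month 24) to T6, T8 and T10 (months 36, 48 and 60): 12, 24 and 36 months.
- From T2 (month 12) to the same visits: 24, 36 and 48 months.

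**The case against.** The strongest reply is that a lagged design was meant. A mediator measured before the outcome is the normal order for mediation. Aims and hypotheses expects early gains in reflective functioning to predict later symptom and self-injury reductions. On that view the 18 late primary-outcome analyses lack a statement of timing, not data. This stands: a reader might infer that the third hypothesis cannot be tested at the late visits, or that carrying the T4 mediator forward is the only workable version. Neither follows. T2 values exist too, the early-change hypothesis arguably points to them, and the third hypothesis names no visits. What does not stand is that the lag can be left unsaid. The Mediation analysis section names no lag, no mediator visit and no covariates, and a lag cannot rescue secondary outcomes that are not collected.

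A second reply is that the scope wording should be read together with the sections that confine work after T4 to primary outcomes. That is reasonable, and it takes the share with no outcome from 43% to zero. It leaves 18 of 60 analyses without a same-visit mediator and without a defined alternative.

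A reader might also infer that the late visits carry a special risk of false mediation. A patient who is better at T4 may score better on the mediator then and simply stay better. The mechanism is real, but the schedule mismatch does not create it. A mediator that is only a by-product of symptoms can mislead a same-visit Sobel test at T2 or T4 in the same way, so this is no argument against T6, T8 and T10 in particular.

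**Conclusion.** Wrong as written. The contradiction between the mediation visit list and the measurement schedule is plain and needs no assumption: at three of five listed visits (60%) no mediator is measured. The share that also has no outcome depends on the reading. It is 45 of 105 (43%) if the scope wording is literal and the seven outcomes of the Design section are used, with a range of 37.5% to 45% under other counts in the article. It is zero if late work is confined to primary outcomes, where 18 of 60 (30%) still lack a same-visit mediator.

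The late secondary-outcome analyses cannot be run under the stated schedule. The late primary-outcome analyses can be run, but only once a lag is defined. The consequence is confined to the explanatory third hypothesis. The planned consultation with a statistician, noted in Limitations and challenges, gives an occasion to correct the text but does not itself resolve the conflict.

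**What to change.** In the Mediation analysis section:

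1. Limit same-visit mediation to T2 and T4.
2. Remove the secondary outcomes from T6, T8 and T10.
3. Either delete mediation at T6, T8 and T10 or define it, for the primary outcomes only, as lagged on one stated mediator measurement. T0–T2 change fits the early-change hypothesis; T0–T4 change is the alternative. Adjust for the baseline outcome and the baseline mediator.
4. State that mediator change after T4 is not observed.

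Adjustment for the T4 outcome should not be mandatory. It guards against persistence of symptoms being read as mediation, but it also removes any true mediation already expressed in T4 symptoms. It is at most a sensitivity analysis, with that trade-off stated.

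The cost is wording only, with no new data. The downside is fewer mediation results, and the long-term ones speak only to mediator change by month 24 at the latest. If same-visit mediation at years 3 to 5 is really wanted, Table 1 would have to change instead. That means more data collection and runs against the stated reason for shortening the late interviews.
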